# Background

Every year over 4 million babies die in the first four weeks of life (the neonatal period) globally. Of these deaths, three million occur in the first seven days (early neonatal period).1-3 Ninety-eight percent of all neonatal deaths occur in developing countries where the risk of neonatal death is six times higher than in developed countries.1 Neonatal death rates are high in remote rural areas, where access to maternal and newborn health services, including skilled health professionals, is limited.4 The most common causes of early neonatal deaths are complications of pregnancy or childbirth, preterm birth, congenital malformations and infections or neonatal sepsis.1 Small for age or low birth weight infants are at higher risk of dying from infections than normal birth weight or appropriate for age infants.5 Preterm birth (babies born at less than 37 completed weeks gestation) and low birth weight (infants born weighing less than 2500g; <1500g birthweight is defined as very low birth weight) are two main factors that significantly contribute to neonatal mortality.1 Preterm birth is associated with delayed development, but evidence about the outcomes of those surviving the neonatal period is scarce.6 A systematic review that found 197 studies measuring outcomes of preterm birth in low and middle income countries found that only 16% were performed in community settings, 19% assessed developmental outcomes, none was done in the Pacific Region, and only 11% fulfilled criteria for high quality.6

Simple, affordable tools to assess gestational age and birth weight would help to identify newborns that may need referral for further assessment or urgent interventions. There are several methods for assessing gestational age during pregnancy, and this includes last menstrual period, fundal height, or ultrasound scan (USS) before 22 weeks of gestation. Neonatal gestational age can be estimated from either the Dubowitz (22 clinical factors)7 or Ballard score (12 clinical factors).8 However, a major challenge, particularly in resource-limited settings, is that for such diagnostic tools, skilled health workers, or complex equipment, or both, are usually needed to assess gestational age accurately.8

For women who give birth in rural and remote areas or in the absence of skilled healthcare personnel, preterm birth and low birth weight are difficult to assess and weighing scales are not always available. Several studies have examined a range of anthropometric measures, which can be assessed easily in resource-limited settings, as proxies for preterm birth and low birth weight.9-11 These studies compared the accuracy of these anthropometric measures with more accurate, reference standards (e.g. USS for gestational age and digital scales for birth weight). Some studies suggested that chest circumference, followed by either mid upper arm circumference (MUAC) or head circumference are highly predictive of low birth weight and preterm birth.9-12

Foot length is another measurement that correlates well in determining preterm birth and low birth weight in several countries in sub Saharan Africa and South Asia, but there have been no similar studies in the Pacific Region.13-20 Foot length is simple to measure with a ruler or tape measure, items which could be readily available in the community and health facility. Studies conducted to date have suggested different cut-offs for foot length that predict preterm birth or low birth weight, ranging from 6.8cm by Hadush et al. in Ethiopia (2017) to 8.0cm by Marchant et al. in Tanzania (2010 and 2014).12,18-19 However, these studies differed in the way in which gestational age was assessed, as well as in the definitions of preterm birth and low birth weight and the method for measuring foot length.8-16,18-21 Nabiwemba et al. found that a hard plastic ruler was more accurate than a flexible tape measure or a printed foot print.15

Papua New Guinea (PNG) had the highest infant mortality rate 50-59 per 1000 births in a 2014 Pacific Islands report.22 An estimated 56% of women in PNG give birth unsupervised, the majority in their villages.23 Health extension officers, nurses, nursing officers and community health workers are trained to measure fundal height during pregnancy to assess gestational age, and to take other anthropometric measurements. If simpler methods, such as foot length, could be used to assess gestational age and birth weight, village birth attendants or village reporters could be trained to do such measurements, which may facilitate referral of vulnerable newborns for further management and help to reduce neonatal and infant mortality in rural PNG.

The Women And Neonatal Trial of Antenatal Interventions and Management (WANTAIM) is a randomized cluster crossover trial of the effectiveness of point-of- care testing for sexually transmitted infections in pregnancy to improve birth outcomes. The prevention of adverse outcomes, such as preterm birth, low birth weight, neonatal eye infections and neonatal pneumonia should contribute to improved infant health. The trial enrols women attending antenatal clinics and includes assessment of gestational age by USS and neonatal examination within 72 hours of birth. This setting allows for assessment of both anthropometric measurements, including foot length, within 72 hours of birth and follow up of physical growth and development outcomes beyond the neonatal period in a community-enrolled sample. Such information will contribute to evidence needed to assess the burden of disease due to preterm birth and low birth weight.6

# Study Objectives

The primary objective of this Neonatal Foot Length (Neofoot) study is to determine the diagnostic accuracy of foot length measurement to predict preterm birth and low birth weight in rural PNG.

Secondary objectives are to:

1. Compare foot length, MUAC and head circumference as predictors of preterm birth and low birth weight
2. Validate a specific foot length cut-off or derive a new cut-off appropriate for PNG
3. Assess the feasibility of using foot length as a measure for preterm birth and low birth weight in the community and health centre by community reporters/volunteers and health centre staff.
4. Determine associations between foot length at birth, physical growth and development of the infant at 6 months, according to study arm.

# Material and Methods

## Study Design

This study will be a prospective cohort study.

## Study setting

The Neonatal Foot Length (Neofoot) study will be conducted as a sub-study of the Women and Newborn Trial of Antenatal Interventions and Management (WANTAIM) in three WANTAIM trial sites in Madang Province.

## Ethics

PNG Institute of Medical Research (PNGIMR) Institutional Review Board with have given ethics approval to this study with IRB number 1811(Appendix1). Ethics approval will also be obtained from Medical Research Advisory Council (MRAC) of the National Department of Health (NDoH) and the University of PNG (UPNG).

## Eligibility criteria

Women enrolled in the two WANTAIM sites will be eligible if they have complete data on USS assessment of gestational age and have a post-natal visit completed within 72 hours of birth. Women whose baby died in the perinatal period, or who have very sick babies or babies with congenital abnormalities that restrict team from collecting outcomes within 72 hours of birth, or who will be moving out of the catchment area within the next 6 months, will be excluded. Locator information for eligible participants, collected at WANTAIM enrolment will be updated.

## Procedures

### Staff training

Community reporters/volunteers and health centre staff will be trained by the paediatric research registrar to measure infant foot length accurately.

All other study-specific training, including measurement of MUAC, weight, length, head circumference, respiratory rate, and heart rate, and completion of Neofoot study CRFs will be conducted by the paediatric research registrar.

### Informed consent procedure

The informed consent procedure for the Neofoot study will be conducted by the paediatric research registrar after completion of the WANTAIM 72-hour post-natal assessment. After assessing literacy, the research registrar will explain the procedures of the Neofoot study to the parent/caregiver (Appendix 2a, English, Appendix 3a, Pidgin) and obtain written consent (Appendix 2b, English, Appendix 3b, Pidgin). If the parent/caregiver is assessed as illiterate, an independent literate witness will be present during the informed consent process to attest that the information was explained accurately, was apparently understood, and that consent was given voluntarily. The parent/caregiver will either put a written mark on the consent form or put their thumbprint onto the consent form. The witness will then sign and date the consent form.

### Post-natal 72 hours and 6 month assessments

At the first post-natal (72 hours) assessment, anthropometric measurements in addition to those collected for WANTAIM will be carried out, either at the health facility or at home. At this time, a follow-up visit will be planned for 6 months later, to take place at a health centre. Table 1 shows the measurements that will be collected at each assessment.

Foot length will be measured using a stiff clear plastic ruler. The right foot will be measured from the heel to the tip of the big toe.18

As part of the 72-hour post-natal assessment, the mother or care giver will also be given post-natal health information about immediate care of her newborn infant. The handheld baby book will be used as a guide to discuss essential care of the baby (cord care, keeping the baby warm, regular breast feeding, immunisation and well clinic schedules at 1 month, 2 months, 3 months, 4 months, 5 months and 6 months), recognising danger signs in newborn and infants and actions to take in the event of these.

The 6-month follow-up visit will be conducted at a health centre or at home if the mother/care giver does not attend the clinic visit. The research registrar will be responsible for assessing the baby and collecting the anthropometric and development data (Table 1) and recording it in the study-specific CRF. Information about growth assessments using World Health Organization growth charts, immunisations, illnesses and hospital admissions in the period between the two visits will be obtained from discussion with the mother/care giver and from the baby book and recorded in the study specific CRF. If the registrar is concerned about a particular aspect of the infant’s development, or if the infant is unwell (including undernourished), the paediatric registrar will follow routine procedures for referring that infant for paediatric review either as an outpatient or an emergency, as the situation warrants. In addition, if the visit takes place in the home, the mother will be advised to attend the child health clinic to update immunisations, as required.

Table 1: Description of procedures at Neofoot study assessments within 72 hours and at 6 months

| **Procedures** | **Description or method** | **Person responsible** | **Neofoot enrolment** |
| --- | --- | --- | --- |
| Eligibility | Assess whether participant satisfies criteria to join the study | Researcher | X |
| Literacy check | Check if the participant is literate. So that steps such as an independent witness can help to ensure the parent fully understands the risk/benefits and requirements of participating tin the study | Researcher | X |
| Informed consent procedure (including flip chart) | Parent/carer of the newborn will be informed about the Neofoot study and procedure. If they wish to join, they will sign the consent form | Researcher | X |
|  | Weight is measured using digital scales | WANTAIM clinical staff |  |
| Foot length measurement | The right foot was measured from the heel to the end of the big toe, using a stiff clear plastic ruler. | Researcher | X |
|  |  |  |  |
|  |  | Volunteer | X |
|  |  |  |  |

Abbreviations: Women And Newborns Trial of Antenatal Intervention and Management

## Possible sources of bias in outcome measurements

Foot length measurement could be biased if the gestational age is known by the person undertaking the foot length measurement. This bias can be minimized by making the gestational age unavailable when foot length is measured. We will also measure foot length before going through other documents (client held record book, admission notes).

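### The foot-length measurer is masked to gestational age only; birth weight, the other primary reference standard, has probably been taken already and no step withholds it

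*Protocol*

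**What the plan says.** The Protocol (Study Objectives) sets one primary objective with two targets, preterm birth and low birth weight. Statistical analysis names the two reference standards: ultrasound for gestational age and digital scales for birth weight.

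The section on possible sources of bias in outcome measurements names one mechanism: "Foot length measurement could be biased if the gestational age is known by the person undertaking the foot length measurement". It gives one remedy: "This bias can be minimized by making the gestational age unavailable when foot length is measured". It then adds a rule of sequence, that the foot is measured before the client-held record book and the admission notes are consulted. Weight does not appear in that section.

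Three other places bear on the point:

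- Under Eligibility criteria, women "will be eligible if they have complete data on USS assessment of gestational age" and have had the post-natal visit in time. Table 1 gives the eligibility step ("Assess whether participant satisfies criteria to join the study") to the 'Researcher'. It gives foot measurement to the 'Researcher' too, with a 'Volunteer' as a second measurer.
- Under Informed consent procedure, sub-study consent is "conducted by the paediatric research registrar after completion of the WANTAIM 72-hour post-natal assessment".
- In Table 1, "Weight is measured using digital scales" is the task of WANTAIM clinical staff, with no mark in the Neofoot enrolment column.

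**The concern.** In a diagnostic accuracy study the index test should be read without knowledge of the reference result. The protocol accepts this for gestational age. The same reasoning applies to weight, because a measurer who knows that the baby is below 2500 g may read a borderline foot as shorter. The reading is taken by eye from a plastic ruler and analysed in 1 mm steps, so a small shift in rounding can move a baby across a cut-off.

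Such a bias would favour the test. It would raise sensitivity, specificity and AUC for low birth weight and could move the recommended cut-off. It arises when the reading is written down, so no later analysis can remove it. It therefore has to be settled in the procedures and cannot be left to an analysis plan.

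**Working it through.** The protocol gives no figure on this point, so there is none to reproduce. The check sets the sections side by side and then illustrates a possible size.

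**What is withheld, and from whom**

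| Reference standard | Stated masking | Possible route to the measurer |
|---|---|---|
| Ultrasound gestational age | To be unavailable at foot measurement; record book and notes read afterwards | The eligibility check, done by the same role, needs ultrasound data to be complete |
| Digital-scale weight | Not named; record book and notes read afterwards | Weighing by WANTAIM staff, probably completed before the foot is measured |

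**Order of events**

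1. The registrar takes sub-study consent once the WANTAIM 72-hour assessment is complete.
2. Foot length is a sub-study procedure, so it follows consent and hence that assessment.
3. Weight belongs to WANTAIM staff and is not marked as an enrolment procedure of the sub-study. The text before Table 1 says that the sub-study's measurements are additional to WANTAIM's.
4. The natural inference is that weighing precedes foot measurement. No sentence says so outright.

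**Illustration 1: AUC.** Assumptions not in the documents: SD of foot length 4 to 5 mm, and readings in affected babies pulled down by 0.5 or 1 mm on average. With AUC = Φ(d/√2), an AUC of 0.80 gives d = √2 × Φ⁻¹(0.80) = 1.19 SD.

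- A 1 mm pull adds 1/5 = 0.20 to 1/4 = 0.25 SD. AUC becomes Φ(1.39/√2) = 0.837 to Φ(1.44/√2) = 0.846.
- A 0.5 mm pull adds 0.10 to 0.125 SD. AUC becomes 0.819 to 0.824.
- From a starting AUC of 0.85, a 1 mm pull gives 0.881 to 0.887.

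If only a fraction f of the affected babies' readings is unmasked, AUC = (1 − f) × 0.80 + f × (shifted AUC). For a 1 mm pull, f = 0.5 gives about 0.82 and f = 0.25 about 0.81. With f = 0 there is no gain.

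**Illustration 2: sensitivity.** Suppose that knowing the reference result moves a fraction f of the missed babies to the right side of the cut-off. Then the observed sensitivity is s + f(1 − s).

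- s = 70%: f = 5% gives 70 + 0.05 × 30 = 71.5%; f = 20% gives 70 + 0.20 × 30 = 76%.
- s = 90%: f = 5% gives 90 + 0.05 × 10 = 90.5%; f = 20% gives 90 + 0.20 × 10 = 92%.

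The gains run from 0.5 to 6 points. The Sample size section states a precision of 4 to 5 points either way. Only the upper end, at 70% sensitivity, exceeds that.

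**The case against.** The case on the other side has four parts, and much of it stands.

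- **Gestational age is already addressed.** A reader might infer that the eligibility check contradicts the masking. The documents do not support that. The criterion is that "they have complete data on USS assessment of gestational age", and one can confirm that dating is complete without seeing the value. What remains is a risk, because one role does both tasks and no way of separating them is described.
- **Weight is not wholly unprotected.** A reader might infer that the low-birth-weight half of the objective has no safeguard at all. That is too strong. The record book and admission notes are plausible places for a birth weight to be written, and they are opened only afterwards. Different staff do the weighing, and nothing says that the measurer watches the scale or receives the form. Even so, the rule does not hide a weight just taken by WANTAIM staff.
- **The order and the roles are inferred.** Table 1 is damaged in the text available: the weight row has lost its label and its timing is blank. That the 'Researcher' is the registrar rests on both being assigned consent. The 'Volunteer' has no eligibility role, although no masking to weight is stated for that measurer either.
- **Masking can never be complete.** Anyone measuring the foot sees how small the baby is, so withholding the number removes only part of the expectation. A known weight near 2500 g still adds information where classification turns on it.

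**Conclusion.** The point holds for birth weight. It is a reference standard for the primary objective, the bias section does not name it, and the stated sequence probably places weighing before foot measurement with nothing to withhold the result. The sequence rule on documents gives partial protection only.

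For gestational age the finding is a risk to the stated masking. The documents do not establish that the foot will be read in knowledge of either reference standard.

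The size of any bias cannot be learned from the documents. The rise in AUC from 0.80 to about 0.82 to 0.85 rests on an assumed pull and an assumed SD, falls towards zero as fewer readings are unmasked, and could not all be removed by masking the number. The case for acting rests on the direction of the bias, the impossibility of correcting it later, and the low cost of preventing it.

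**What to change.** Amend the section on possible sources of bias as follows:

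1. State that gestational age and weight are both unavailable to every foot-length measurer, researcher and volunteer alike, until foot length is written on the CRF.
2. Have WANTAIM staff keep the weight form and the scale reading out of view until then.
3. Pass ultrasound eligibility to the researcher as a yes/no flag that dating is complete, without gestational age or due date.
4. Add a CRF tick-box for whether the measurer knew either value, and a supportive accuracy analysis restricted to masked readings.

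This should need no additional staff, but it is not free. WANTAIM staff must hold back the weight form and supply the flag. The masked subgroup rests on self-report and may be small or selected, so its analysis can only support the main one. Consenting and measuring the foot before weighing is not proposed: it would reverse the stated order and put sub-study consent ahead of the parent trial's assessment.

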## Statistical analysis

I will examine the distributions of each variable. I will describe continuous variables using histograms, mean and standard deviation, and median and interquartile range. I will describe frequencies of categorical variables as percentages. I will conduct a descriptive analysis to examine associations with preterm delivery and low birth weight, including social and demographic factors (collected during WANTAIM assessments) and achievement of developmental milestones at 6 months and between study arms and achievement of developmental milestones at 6 months. I will assess the correlation between the gestational age at birth (measured by USS) and birthweight (measured using digital scales) and anthropometric measures (foot length, head circumference, MUAC) using Spearman’s rank correlation coefficient.

I will calculate diagnostic performance of foot length as: a) sensitivity (proportion of newborns correctly identified as preterm, low birthweight or very low birth weight); and b) specificity (proportion of newborns correctly identified as not preterm or not low birth weight) for 1mm increments in foot length. I will also calculate sensitivity and specificity for head circumference (1.0cm increments) and MUAC (1mm increments).8

To assess the diagnostic performance of each anthropometric measure as a predictor of preterm birth, low birth weight and very low birth weight, I will construct receiver operating characteristic (ROC) curves.24 The ROC curve is a graphical plot of sensitivity (vertical axis) against 1 minus specificity (horizontal axis) for each increment in measurement of the anthropometric measure. The best cut-off for each measure is the value at which the sensitivity and specificity are highest. I will then calculate the area under the curve (AUC, with 95% confidence intervals) as a proportion of the total area. The closer the AUC value is to one, the better the predictive value.

I will provide the best cut-off for the prediction of preterm birth, low birth weight and very low birth weight using foot length, head circumference and MUAC. I will recommend the most appropriate and simple measure based on my findings.

I will use linear regression to examine associations between the foot length at birth and achievement of developmental milestones, with multivariable models to control for potential confounding.

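### The masking and order-of-measurement safeguards are written for foot length only, although MUAC and head circumference are competing index tests in the planned comparison

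*Protocol*

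**What the plan says.** The only text on masking is the protocol section Possible sources of bias in outcome measurements. It names the bias for one reading: "Foot length measurement could be biased if the gestational age is known by the person undertaking the foot length measurement". The first safeguard is "This bias can be minimized by making the gestational age unavailable when foot length is measured". The second fixes the order of work: "We will also measure foot length before going through other documents (client held record book, admission notes"). MUAC and head circumference are not mentioned in that section.

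Both are index tests in the same study. Secondary objective 1 (Study Objectives) is to "Compare foot length, MUAC and head circumference as predictors of preterm birth and low birth weight". The Statistical analysis section treats them in parallel with foot length: "I will also calculate sensitivity and specificity for head circumference (1.0cm increments) and MUAC (1mm increments"), followed by ROC curves, AUCs and best cut-offs for all three. It ends the comparison with "I will recommend the most appropriate and simple measure based on my findings".

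**The concern.** A comparison of index tests is fair when the tests are read under the same conditions. Here the protocol recognises that a reader's knowledge of gestational age can distort a measurement, protects one test against it, and is silent on the other two. It gives no reason why a tape reading of the arm or head would be less open to expectation than a ruler reading of the foot.

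If the comparators were read with gestational age known and foot length was not, readings shaded towards expectation would widen the apparent gap between preterm and term infants for the comparators alone. At stake are secondary objective 1 and the final recommendation. The primary objective, the accuracy of foot length itself, does not depend on how the other two measures are read.

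**Working it through.** The protocol states no figure on this point, so there is nothing to reproduce. The check is mainly one of setting sections side by side.

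**What is protected.**

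| Measure | Gestational age withheld from reader | Read before records are opened | Birth weight withheld from reader | Used in comparison and recommendation |
| --- | --- | --- | --- | --- |
| Foot length | Yes | Yes | Not stated | Yes |
| MUAC | Not stated | Not stated | Not stated | Yes |
| Head circumference | Not stated | Not stated | Not stated | Yes |

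The second to fourth columns come from Possible sources of bias in outcome measurements; the last comes from Study Objectives and Statistical analysis.

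**Whether the information exists at the visit.** It does. Eligibility requires "complete data on USS assessment of gestational age". The sub-study also starts late in the visit: "The informed consent procedure for the Neofoot study will be conducted by the paediatric research registrar after completion of the WANTAIM 72-hour post-natal assessment". The record book and admission notes are evidently expected to be consulted, since the protocol sets an order relative to them. A team could therefore follow the text to the letter by measuring the foot, opening the records, and then taking the two tape readings.

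**What a shift would do (illustration with assumed values).** Take a binormal marker with equal variances:

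- True AUC = Φ(d/√2), so d = √2 · z(AUC).
- If expectation adds s SD to the separation between cases and non-cases, apparent AUC = Φ((d + s)/√2).

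| True AUC | d | s = 0.1 SD | s = 0.2 SD |
| --- | --- | --- | --- |
| 0.80 | √2 × 0.842 = 1.190 | Φ(1.290/√2) = 0.819 | Φ(1.390/√2) = 0.837 |
| 0.75 | √2 × 0.674 = 0.954 | Φ(1.054/√2) = 0.772 | Φ(1.154/√2) = 0.793 |

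On these assumptions two equally good measures would appear to differ by about 0.02 to 0.04 in AUC. Both the baseline AUCs and the shift are assumed; the protocol gives neither.

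**Two targets.** For preterm birth the withheld item, gestational age, is the reference standard, so unequal protection acts directly. For low birth weight the reference standard is weight, which is withheld for none of the three measures. There any inequality is only indirect, through gestational age.

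**The case against.** The strongest reply is that this rests on silence. No section says that MUAC or head circumference will be read after the records are opened or with gestational age known. In the available text Table 1 is incomplete and shows no rows for these two measures, so who takes them and when cannot be seen. In practice all three may be taken in one sitting before any document is read, and then they are equally protected. This stands. A reader might infer that the comparators will be read unmasked, or that the comparison is already unfair; the documents support neither.

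Second, the tilt needs foot length to be truly masked. Table 1 assigns the eligibility check to the researcher, who also measures foot length, and that check covers ultrasound data. If the foot-length reader already knows gestational age, all three readings are exposed alike and the tilt largely disappears. This also stands, so the direction is conditional.

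Third, the recommendation is to weigh suitability and simplicity as well as accuracy, so a small AUC gap need not decide it. That limits the consequence without removing it.

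Fourth, some comparator values may come from the WANTAIM examination, which is finished before Neofoot consent. The sub-study may be unable to reorder those readings, so the change cannot be called free in every case.

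One reply does not hold: that the matter can wait for a statistical analysis plan. Masking and order of measurement are field conduct, and an analysis plan cannot mask readings already taken.

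**Conclusion.** The point holds as a gap in a safeguard that the protocol itself considers necessary. Both protections are confined to foot length, while two competing index tests that feed secondary objective 1 and the recommendation have none stated. The text therefore permits the tape readings to be taken with gestational age in view.

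The bias is possible, not shown. It requires that the comparators are in fact read after the records are seen and that foot length is in fact read masked. Under both conditions the preterm comparison would lean towards MUAC and head circumference by an amount the documents do not give; 0.02 to 0.04 in AUC is only what an assumed shift of 0.1 to 0.2 SD would produce. It would be too strong to extend one tilt across the low-birth-weight comparison as well, or to carry the concern to the primary foot-length estimate. The change is worth making because it is cheap and can only be made before data are collected.

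**What to change.** Reword Possible sources of bias in outcome measurements so that foot length, MUAC and head circumference are all measured and written on the CRF before any record is opened, with gestational age unavailable to the reader. Add a matching instruction on the CRF.

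As a separate point, since weight is at present withheld for none of the three, require the readings to be recorded before the birth weight is seen where that is practicable.

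If a comparator value comes from the WANTAIM examination and cannot be reordered, record who read it and what they knew. Report the comparison with that limitation, and add a sensitivity analysis without those values where enough data remain.

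The cost is a fixed order of work at the visit and the CRF instruction. Where values come from the parent trial, there is also the extra recording and possibly a smaller sensitivity analysis.
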